**Power Calculation**

Amongst the 43,000 GTZ exposed patients identified for the feasibility count, 144 were first diagnosed with PD after starting a GTZ. Using STATA 12, we estimate we will have 99% power to detect a 30% reduction in PD incidence amongst GTZ users, if we match each exposed patient to five unexposed. Power to detect a 25% and 20% reduction will be and 91% and 71% respectively. We believe an effect size of 25% would represent a clinically meaningful association, and may also be plausible, given the near complete protection identified in animal studies (Sadeghian et al, 2012).

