**Selection of Comparison Group**

Each GTZ exposed patient will be matched by age, sex, and practice with up to 5 patients receiving other oral treatment for diabetes (unexposed group). To reduce the possibility of confounding, we will only select patients who have also received oral antidiabetic treatments, thus reducing the difference in disease stage between GTZ users and non-users. GTZ prescribing has evolved during >10 years according to changes in treatment guidance and changes made to the licensed indication. Initially they were mostly used as second line combination treatment, but were subsequently also used at earlier stages of diabetes treatment. Rosiglitazone was eventually suspended due to cardiovascular safety concerns and pioglitazone use has waned due to concerns over the risk of bladder cancer. To be considered for inclusion, only patients present in the database from 1999 onwards and with at least 12 months UTS follow up prior to prescribing events that trigger eligibility will be included. For instance a patient could be matched to a GTZ user in category 1) above if they had never received an OAD before 1999 and began taking a sulphonylurea with no other OAD after at least 12 months UTS follow up. Follow up for the unexposed will begin at the first prescribing event that makes them eligible for inclusion.

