**Limitations of the Study Design, Data Sources and Analytic Methods**

Diagnoses of PD in the CPRD have a positive predictive value of 90% (Becker et al, 2008) and so a small degree of misclassification amongst outcomes is expected. However, this is likely to be non-differential with respect to GTZ exposure and would be expected to bias results towards the null. In addition, missing cases of PD are likely to be rare in our study population, given that the prevalence of PD is low in the general population. Misclassification of the exposure is also likely to occur to some degree, with patients not being completely adherent to prescribed medicines. However, diabetes is a serious condition for which patients are likely to be motivated to take their medication, and substantial misclassification is not anticipated. Again, misclassification is unlikely to be differential with respect to PD status and so a dilution of any effect towards the null would be expected.

Whilst a small number of risk factors for PD are known and will be accounted for in the design and analysis (e.g. age, sex, smoking), it is not anticipated that these factors will be strongly associated with the choice to prescribe a GTZ, and so confounding is not expected to be strong in this study. Nonetheless, the analysis plan ensures potential confounding will be addressed, and in particular the separate and potentially additive effects of GTZs and metformin will be assessed.

Since the study is conducted entirely within the population with diabetes, the generalisability of results may be affected. However, it is unlikely that any pharmacological effect of GTZs relevant to PD would be limited to people with diabetes only.

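### The stated 99%, 91% and 71% power holds for recorded PD diagnoses; at the protocol's own 90% predictive value, power for a true 25% reduction in PD is about 83–86%

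*Protocol*

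**What the plan says.** The Power Calculation section starts from a feasibility count: "Amongst the 43,000 GTZ exposed patients identified for the feasibility count, 144 were first diagnosed with PD after starting a GTZ". It then gives the three power figures: "Using STATA 12, we estimate we will have 99% power to detect a 30% reduction in PD incidence amongst GTZ users", and "Power to detect a 25% and 20% reduction will be and 91% and 71% respectively". The matching ratio is stated as a condition: "if we match each exposed patient to five unexposed". The target is named as well: "We believe an effect size of 25% would represent a clinically meaningful association". It is called plausible because of neuroprotection seen in animals, so the effect in mind is one on the disease.

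The Limitations section gives the quality of the outcome record: "Diagnoses of PD in the CPRD have a positive predictive value of 90" (per cent). It adds that the misclassification is probably unrelated to glitazone exposure and would bias the result towards no effect.

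Exposures, Outcomes and Covariates defines the outcome as a first recorded PD code after the index date. Under Statistical Analysis, confirmation by at least two anti-Parkinson's prescriptions is a sensitivity analysis only.

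**The concern.** The power paragraph speaks of a reduction in PD incidence, but its event count is of recorded diagnoses. The protocol's own predictive value separates the two: of 144 recorded diagnoses, about 14 (0.10 × 144 = 14.4) would not be PD, and an effect of glitazones on PD cannot prevent those. The primary analysis keeps them, so the rate ratio it estimates lies closer to 1 than the rate ratio for PD. The Limitations section states the size and direction of this dilution, yet the power figures allow for neither.

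The protocol calls the study hypothesis testing, and the Background says its results should help decide where further clinical research is directed. A null result read against 91% power would look like stronger evidence against a 25% effect on PD than the design can give.

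**Working it through.** **Inputs from the protocol.** Exposed n = 43,000; recorded PD events in the exposed = 144; five comparators per user; reductions of 30%, 25% and 20% (Power Calculation). Predictive value 90%, non-differential, bias towards the null (Limitations).

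**Assumptions.** Two-sided 5%: the protocol gives no significance level, and a one-sided test does not reproduce its figures (99.6/96.0/82.0%). The 90% applies to these events. False positives arise at the same rate in both groups and are not affected by glitazones.

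**Formula.** Two-proportion normal approximation with k comparators per user:

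- pe = 144/43,000 = 0.003349; pu = pe/RR; p̄ = (pe + k·pu)/(1 + k)
- s0 = √[p̄(1 − p̄)(1/n + 1/(kn))]; s1 = √[pe(1 − pe)/n + pu(1 − pu)/(kn)]
- power = Φ[(pu − pe − 1.96·s0)/s1]; the continuity-corrected form first subtracts ½(1/n + 1/(kn)) from pu − pe.

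**Step 1: reproduce the stated figures (k = 5, no dilution).** For RR 0.75, pu = 192/43,000 = 0.004465, s0 = 0.0003448, s1 = 0.0003135. Then (0.001116 − 0.000676)/0.0003135 = 1.405, so power is 92.0% (91.3% with continuity correction). The three figures are 99.0/92.0/71.8% uncorrected and 98.9/91.3/70.3% corrected, against 99/91/71% stated. A Wald test on the log rate ratio gives 98.0/89.6/70.1%, also close. Treating 144/43,000 as the comparator risk gives 94.5/82.3/61.5% and does not match.

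**Step 2: dilute the rate ratio.** With equal false-positive rates, the predictive value cannot be exactly 90% in both groups when true PD rates differ, so both placements are shown.

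- 90% among users: 129.6 true and 14.4 false events. Comparator events per 43,000 = 129.6/0.75 + 14.4 = 187.2, so observed RR = 144/187.2 = 0.769.
- 90% among comparators: observed RR = 0.9 × 0.75 + 0.1 = 0.775.

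The corresponding values for true RR 0.70 are 0.722 and 0.730; for 0.80 they are 0.816 and 0.820.

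**Step 3: power at 5:1 with dilution.** For a true 25% reduction with 90% among users, pu = 187.2/43,000 = 0.004353, s0 = 0.0003411, s1 = 0.0003127, z = 1.075, power 85.9%. With 90% among comparators, z = 0.979, power 83.6%.

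| True reduction | Stated | 90% among users: uncorrected (corrected) | 90% among comparators: uncorrected (corrected) |
|---|---|---|---|
| 30% | 99% | 97.3% (97.0%) | 96.1% (95.7%) |
| 25% | 91% | 85.9% (84.9%) | 83.6% (82.5%) |
| 20% | 71% | 62.8% (61.1%) | 60.7% (59.0%) |

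On the Wald version, 89.6% for the 25% effect becomes 83.4% or 81.2%, a fall of similar size.

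**Step 4: true effect needed for a recorded 25% reduction.** Comparator version: (0.75 − 0.1)/0.9 = 0.722, a 27.8% reduction. User version: 0.9/(1/0.75 − 0.1) = 0.730, a 27.0% reduction.

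**Step 5: matching ratio (mean assumed; the protocol gives none).** Uncorrected power for a true 25% reduction:

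| Mean ratio | No dilution | 90% among users | 90% among comparators |
|---|---|---|---|
| 5:1 | 92.0% | 85.9% | 83.6% |
| 4:1 | 90.9% | 84.5% | 82.1% |
| 3:1 | 89.1% | 82.1% | 79.7% |

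**The case against.** The best defence is that nothing was miscalculated. The outcome is a recorded diagnosis, the 144 are recorded diagnoses, and the Poisson model estimates a rate ratio for recorded diagnoses. For a 25% reduction in that quantity, 91% is right. This stands, and anyone who infers an arithmetic slip is mistaken. It does not rescue the wording, because the paragraph claims power for a reduction in PD incidence and justifies its 25% target by an effect on the disease.

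A second defence is that the bias is disclosed and a sensitivity analysis with a stricter case definition is planned. Both are true, and both help interpretation, but neither changes the power quoted for the primary analysis.

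Third, the 90% comes from a cited study that is not at hand, and whether it carries over to the Appendix 2 code list cannot be checked. That is a fair limit. The figures here are conditional on it, but it is the value the protocol itself adopts.

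A reader might also infer that the matching ratio contradicts the design, since Selection of Comparison Group says "Each GTZ exposed patient will be matched by age, sex, and practice with up to 5 patients". It does not: five is an openly stated condition and the other is an upper limit, so the two are compatible. Nor do the documents support quoting power of about 80%. That needs a mean of about three comparators, a figure the protocol does not contain.

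**Conclusion.** The point holds in a limited form. The stated 99/91/71% are correct for reductions in recorded PD with five comparators per user and too high for reductions in PD itself. On the protocol's own 90% predictive value, power at 5:1 is about 96–97%, 83–86% and 59–63% for true reductions of 30%, 25% and 20%. The chance of missing the named 25% effect rises from 9% to about 14–17%.

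This rests on a two-sided 5% test, on the 90% applying to these events, and on false positives that are equally frequent in both groups. If the mean ratio fell below five, the further loss for the 25% effect would be about 1 point at 4:1 and 3–4 points at 3:1; that is an assumption to note, not a separate fault. It would be wrong to conclude that the design is inadequate: by this calculation, power for the 25% target stays above 80% at 5:1, and the sample is every eligible user in the database, so power does not set its size.

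**What to change.** In the Power Calculation section, do one of two things:

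- Restate power for true reductions in PD of 30%, 25% and 20% as about 96–97%, 83–86% and 59–63% at five comparators per user. Give the two-sided 5% level and the 90% predictive value as assumptions.
- Keep 99/91/71%, but say that they refer to reductions in recorded diagnoses, and that a 25% reduction in recorded diagnoses corresponds to a true reduction in PD of about 27–28%.

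Optionally, add a sentence on what a lower achieved matching ratio would cost, marked as an assumption.

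The cost is the rewording of one paragraph and a less favourable headline figure. No patients, data or analyses are added.

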**Exposures, Outcomes and Covariates**

Exposure will be determined by prescribing records, using code lists for individual OADs. Code lists for GTZs can be found in Appendix 1. The index date for each patient will be their first prescribing event that qualifies them for study entry (e.g. first exposure to a GTZ)

The outcome for this study is the first recording of a PD diagnosis after the index date, as identified from clinical and referral records, using the Read code list in Appendix 2. PD due to known causes will be excluded based on the recording of codes presented in Appendix 2.

Covariates to be explored due to their possible association with PD and potential confounding nature will be:

- Smoking status determined using the additional clinical details file
- HRT use determined using prescribing records
- Head trauma as determined by Read code recording
- Age and sex will be accounted for through matching
- Calcium channel blocker use as determined by prescribing records: This exposure has been shown to reduce the incidence of PD (Becker et al, 2008).
- Diabetes itself has been shown to be possibly associated with PD (Wahlqvist et al, 2012). Length of time between diabetes diagnosis and index date, and HbA1c level at index date will be determined and explored for possible confounding properties. In addition, the effect of time updated HbA1c levels will be explored.
- Metformin has been suggested to also have a protective effect against PD (Wahlqvist et al, 2012). As a very commonly prescribed diabetes medication, this will be explored in detail as described below under “Statistical Analysis”.

Other covariates that have not been shown to be associated with PD will also be explored in case of possible confounding, and will include:

- Alcohol consumption
- Body mass index
- Calendar year

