**Statistical Analysis**

We will measure an incidence rate ratio for the association between GTZ use and incident PD using poisson regression, comparing patients exposed to GTZs with patients exposed to alternative treatments. The primary analysis will follow all patients from their index date until the earliest of a PD record, transfer out/death, or last collection date for the practice, and their exposure will remain as defined at the index date, regardless of any subsequent changes in therapy (analogous to an intention to treat analysis in a clinical trial). Secondary analyses will be as follows:

- Censoring follow up at end of GTZ therapy, defined as last prescription plus 90 days, followed by at least 180 days GTZ-free follow up time.
- Stratified analysis based on metformin and GTZ treatment status, to explore the individual and any additive effects of both treatments. Whilst we anticipate most patients will be exposed to metformin, we anticipate a sizeable population who will not receive metformin.
- We have chosen to measure the incidence of PD from the start of therapy with GTZs as the pre-clinical work to date suggests a fast onset of any protective effect. Whether this effect varies with exposure length will be assessed through a stratified analysis on length of follow up after starting GTZ therapy.
- Sensitivity analysis defining PD as a Readcode indicating PD plus at least 2 prescriptions for an anti-Parkinson’s drug, to reduce the likelihood of outcome misclassification. Although cases with little follow up beyond their diagnosis will be excluded, this approach will only reduce study power, but will reduce misclassification bias. The date of earliest recorded diagnosis will remain the date of the outcome.
- Sensitivity analysis to look separately at the effects of pioglitazone and rosiglitazone.
- Sensitivity analysis adjusting for all variables identified as potential confounders, in addition to those included in the forward stepwise modelling strategy (see below).

Adjustments for potential confounding will be made in a forward stepwise manner retaining variables in the model if they have a substantial impact on the estimated rate ratio (a change of 10% or more), and starting with variables that have the greatest effect on PD incidence in univariate analyses. All data management and analyses will be performed using Stata 12 (StataCorp, Texas).

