**Appendix 2: Codes used to identify Parkinson’s Disease**

Parkinson’s disease with no identified cause

| medcode | readterm |
| --- | --- |
| 1691 | paralysis agitans |
| 4321 | parkinson's disease |
| 8956 | parkinsonism with orthostatic hypotension |
| 9509 | [x]dementia in parkinson's disease |
| 10718 | o/e - parkinsonian tremor |
| 14912 | parkinson's disease nos |
| 16860 | o/e - parkinson gait |
| 17004 | o/e - parkinson posture |
| 53655 | o/e -parkinson flexion posture |
| 59824 | o/e-festination-parkinson gait |
| 86062 | [x]parkinsonism in diseases classified elsewhere |
| 96860 | cerebral degeneration in parkinson's disease |

Parkinsonism with identified causes

| medcode | readterm |
| --- | --- |
| 19478 | drug induced parkinsonism |
| 24001 | secondary parkinsonism due to other external agents |
| 26181 | secondary parkinsonism, unspecified |
| 33544 | parkinsonism secondary to drugs |
| 51105 | postencephalitic parkinsonism |
| 52589 | syphilitic parkinsonism |
| 72879 | [x]secondary parkinsonism, unspecified |
| 97170 | [x]other secondary parkinsonism |
| 100128 | vascular parkinsonism |

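### Drug-induced parkinsonism is removed only when a cause code is recorded, and the two-prescription sensitivity analysis tests for treatment and not for cause; the likely result is modest dilution that a cheap restriction in that analysis would check

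*Protocol*

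**What the plan says.** In Exposures, Outcomes and Covariates, the outcome is the first PD record after the index date, "as identified from clinical and referral records, using the Read code list in Appendix 2". The same paragraph adds the exclusion: "PD due to known causes will be excluded based on the recording of codes presented in Appendix 2".

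Appendix 2 holds two lists. The known-cause list has nine codes, of which two name drugs: 19478, "drug induced parkinsonism", and 33544, parkinsonism secondary to drugs. The case list has twelve codes. Five of them are examination findings of tremor, gait or posture that say nothing about cause, for example 10718, "o/e - parkinsonian tremor".

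The covariate list in the same section shows that the prescribing file is already in use, for instance "Calcium channel blocker use as determined by prescribing records", and likewise for HRT and for antidiabetic exposure. No drug that can cause parkinsonism appears there as an exclusion or a covariate.

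Statistical Analysis plans one stricter case definition: "Sensitivity analysis defining PD as a Readcode indicating PD plus at least 2 prescriptions for an anti-Parkinson’s drug". It gives no drug list and sets no condition on cause.

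The Limitations section gives a positive predictive value of 90% for recorded PD diagnoses and says of the resulting error: "However, this is likely to be non-differential with respect to GTZ exposure and would be expected to bias results towards the null".

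**The concern.** The protocol itself treats drug-induced parkinsonism as something other than the outcome of interest. Yet it recognises such a case only if the GP saw the cause and chose one of two codes. If the GP instead entered a general PD code, or recorded a parkinsonian tremor in a patient on a dopamine-blocking drug, the patient counts as an event in the primary analysis.

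The stricter definition does not settle the matter. Its stated purpose is to cut outcome misclassification, but two anti-Parkinson prescriptions show that the patient was treated, not why the signs arose. A drug-induced case that was coded as PD and then treated passes the check. The information that bears on cause, namely earlier prescriptions of drugs that can produce parkinsonism, lies in a file the study already reads.

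At stake is some dilution of the rate ratio, and a confirmed-PD analysis that confirms less than its purpose suggests.

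**Working it through.** **1. The rules side by side.**

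| Case as recorded | Primary outcome | Two-prescription analysis |
| --- | --- | --- |
| Drug-induced, with a drug-cause code | excluded | excluded |
| Drug-induced, coded as PD or as a sign, untreated or treated once | event | not a case |
| Drug-induced, coded as PD, at least two anti-Parkinson prescriptions | event | case |

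The second row is what the check removes. The third is what it leaves.

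**2. The protocol's own power figures.** Inputs from Power Calculation: 43,000 exposed, 144 events among them, five comparators per exposed patient. The exposed risk is 144/43,000 = 0.335%. The significance level is not stated; two-sided 0.05 is assumed. A two-proportion calculation with 0.335% as the exposed risk and 0.335%/RR as the comparator risk gives 99.0%, 92.0% and 71.8% for reductions of 30%, 25% and 20%. With a continuity correction it gives 98.9%, 91.3% and 70.3%. The stated figures are 99%, 91% and 71%, so they reproduce.

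**3. Dilution.** The protocol's meaningful effect is a 25% reduction, so the true rate ratio is taken as 0.75. False-positive events are assumed unrelated to glitazones (rate ratio 1 on them). The drug-induced share is not in the documents, so a range is shown. The 10% row uses the complement of the stated 90% predictive value and attributes every false positive to drugs.

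If a share s of recorded comparator events is non-PD:

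observed RR = 0.75 × (1 − s) + s

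- s = 5%: 0.7125 + 0.05 = 0.763
- s = 10%: 0.675 + 0.10 = 0.775
- s = 20%: 0.60 + 0.20 = 0.80

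If a share f of the 144 recorded exposed events is non-PD:

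observed RR = 1 / [(1 − f)/0.75 + f]

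For f = 10% this is 1/(1.2 + 0.1) = 0.769. Using the power method of step 2 without continuity correction:

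| f | Observed RR | Power, events kept | Power, events removed |
| --- | --- | --- | --- |
| 2% | 0.754 | 91.0% | 91.4% |
| 5% | 0.760 | 89.3% | 90.6% |
| 10% | 0.769 | 85.9% | 88.9% |
| 20% (stress case) | 0.789 | 77.2% | 84.8% |

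The reference without false positives is 0.75 with 92.0% power. At f = 10% about 144 × 0.9 = 130 exposed events remain after removal. The last column is idealised: it removes only false positives, whereas a real prescribing rule would also remove some true cases.

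**4. Size against sampling error.** With equal follow-up, comparator events would number about 5 × 144/0.75 = 960. Then SE(log RR) = √(1/144 + 1/960) = 0.089, and the 95% interval around 0.75 runs from about 0.63 to 0.89. The shift from 0.75 to 0.775 is ln(0.775/0.75)/0.089 = 0.37 standard errors; to 0.769 it is about 0.28.

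**The case against.** The strongest reply is that nothing here contradicts itself. The protocol states a coding rule, implements it with nine codes, adds a stricter case definition, and discloses residual misclassification with its expected direction. A prescribing filter is then a refinement. This largely stands, and it is why the point concerns a sensitivity analysis and not the primary outcome.

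A second reply is that the two-prescription check should not be dismissed. That is right: it drops untreated and once-treated cases. A reader might infer that it shares the weakness in full because anti-Parkinson drugs include agents given for drug-induced signs. The protocol gives no drug list, so which drugs count cannot be checked; such a list may sit elsewhere. What remains is that, whatever the list, the check does not ask about cause.

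A third concerns direction. One might argue that dopamine-blocking antiemetics follow diabetes severity, that severity differs between glitazone users and comparators, and that the error is therefore differential. The documents do not support this chain. Selection of Comparison Group speaks of reducing a difference in disease stage; it reports no known imbalance in severity. Users are classified by treatment stage, the comparator example is matched on that stage, and diabetes duration and HbA1c are planned covariates. Non-differential error is the protocol's assumption and is untested, but nothing in the documents shows it to be wrong.

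Finally, a prescribing rule removes true PD cases too, and could do so unequally between groups if use of these drugs differed by exposure. This stands as a reason not to build the rule into the primary outcome.

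**Conclusion.** The gap is real but modest. Drug-induced cases without a cause code count as events, and the stricter analysis reduces their number without testing for cause. If the whole 10% implied by the stated predictive value were drug-induced and unrelated to exposure, a true ratio of 0.75 would appear as 0.769 to 0.775, and power would fall from 92.0% to about 85.9% on the exposed-event basis. The true drug-induced share is unknown and may be well below that.

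Two assumptions carry the result. One is that false positives are unrelated to glitazone use. The other is that the 90% figure applies to this code list: it is quoted for PD diagnoses, and the protocol does not show that it covers the examination signs, so 10% is not a strict bound. The 20% row shows what a larger share would do.

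A reader might conclude that the error could produce a spurious protective effect, or that the primary result would be invalid. Under non-differential error it cannot create protection; it only pulls the ratio towards 1, as the Limitations section expects.

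**What to change.** Leave the primary outcome as it is. In the sensitivity analysis that already requires two anti-Parkinson prescriptions, add two conditions, applied identically to glitazone users and comparators:

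- A first PD code is not counted as a case, and follow-up ends there, if the prescribing file shows a dopamine-blocking drug (for example an antipsychotic or a dopamine-blocking antiemetic) in a prespecified window before it. Six months is a workable choice, but the documents do not supply a value, so the window must be fixed before analysis.
- Only dopaminergic agents count towards the two prescriptions, with the product-code list written down.

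Read the result beside the primary estimate, not in place of it. The cost is two further product-code lists drawn from data already held, and the loss of some true PD cases, and so of some power, in that sensitivity analysis only.

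### Age and sex are left to matching alone, but the named Poisson model has no matched-set or current-age step, so age confounding can remain in the primary rate ratio

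*Protocol*

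**What the plan says.** On control of age and sex, the covariate list in the Protocol (Exposures, Outcomes and Covariates) says: "Age and sex will be accounted for through matching".

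The section Selection of Comparison Group sets out the matching as follows: "Each GTZ exposed patient will be matched by age, sex, and practice with up to 5 patients receiving other oral treatment for diabetes (unexposed group". In the same section: "Follow up for the unexposed will begin at the first prescribing event that makes them eligible for inclusion".

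On the primary model (Statistical Analysis): "We will measure an incidence rate ratio for the association between GTZ use and incident PD using poisson regression". Follow-up is of variable length: "The primary analysis will follow all patients from their index date until the earliest of a PD record, transfer out/death, or last collection date". The section does not mention the matched set, a conditional or stratified likelihood, an age or sex term, or current age.

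Other covariates enter by a forward stepwise rule, "retaining variables in the model if they have a substantial impact on the estimated rate ratio (a change of 10% or more". A fuller model is planned only as a "Sensitivity analysis adjusting for all variables identified as potential confounders, in addition to those included in the forward stepwise modelling strategy"; age and sex are not named there.

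The Limitations section lists age and sex among known PD risk factors that design and analysis will take into account, but gives no analysis step for them. The content checklist marks both the analysis plan and the plan for confounding as included in this Protocol.

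**The concern.** Matching a cohort balances the matching factors at entry. Whether the balance carries through to an unconditional ratio of events to person-time depends on two further conditions:

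1. **The number of comparators per exposed patient is unrelated to age and sex.** If older patients obtain fewer comparators, the comparator group as a whole is younger than the exposed group, although each set is matched.
2. **Follow-up is similar in the two groups.** A group that is followed longer contributes person-time at older ages, even when entry ages are identical.

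The Protocol secures neither. The matching ratio has a ceiling but no floor, comparators are sought within one practice, and eligibility has no age restriction. Comparators start at their own qualifying prescription, and the Protocol does not align that date with the exposed patient's index date. Follow-up then runs to a variable end.

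The primary rate ratio is at stake. The Power Calculation treats a 25% reduction as clinically meaningful, and an age imbalance could mimic or mask a good part of an effect of that size.

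**Working it through.** **The plan's own figures first.** Inputs from the Power Calculation section: 43,000 exposed, 144 PD cases, five comparators each, reductions of 30%, 25% and 20%. No alpha is given, so I assume two-sided 0.05. The exposed risk is p1 = 144/43,000 = 0.003349 and the comparator risk is p0 = p1/RR. With the pooled two-proportion formula,

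power = Φ[(|p1 − p0| − 1.96·SE0)/SE1],

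where SE0 is the standard error under the pooled risk and SE1 the one under the separate risks. For RR 0.75: p0 = 0.004465, difference 0.001116, SE0 = 0.000345, SE1 = 0.000314, so power = Φ(1.40) = 92.0%. For 0.70 and 0.80 the results are 99.0% and 71.8%. With a continuity correction the three are 98.9%, 91.3% and 70.3%. The Protocol states 99%, 91% and 71%, so its figures reproduce. They presuppose an unbiased rate ratio.

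**Assumptions for the bias, none of them in the Protocol.** True RR = 1. PD incidence rises by a constant proportion b per year of age, with b = 0.08 and a range of 0.06 to 0.10. Entry ages are 45, 55, 65 and 75, with shares 0.2, 0.3, 0.3 and 0.2.

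**Unequal follow-up, full 1:5 matching, identical entry ages.** The mean rate over F years is proportional to (e^(bF) − 1)/(bF).

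- b = 0.08: F = 5 gives 1.230 and F = 7 gives 1.341. With exposed patients followed for 5 years and comparators for 7, the apparent RR is 1.230/1.341 = 0.917.
- b = 0.06: 1.166/1.243 = 0.938.
- b = 0.10: 1.297/1.448 = 0.896.
- Reversed (exposed 7, comparators 5), b = 0.08: 1.341/1.230 = 1.09.

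Conditioning on entry age or on the matched set alone would not remove this. The difference arises after entry, so current age is needed.

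**Ratio related to age, equal follow-up.** The relative rates e^(0.08(age − 65)) are 0.202, 0.449, 1.000 and 2.226. The exposed mean rate is 0.2×0.202 + 0.3×0.449 + 0.3×1.000 + 0.2×2.226 = 0.920.

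| Comparators at 45/55/65/75 | Comparator weights | Comparator mean rate | Apparent RR |
|---|---|---|---|
| 5/5/4/3 | 1.0, 1.5, 1.2, 0.6 (sum 4.3) | 3.411/4.3 = 0.793 | 0.920/0.793 = 1.16 |
| 3/4/5/5 | 0.6, 1.2, 1.5, 1.0 (sum 4.3) | 4.386/4.3 = 1.020 | 0.920/1.020 = 0.90 |
| 4.3 on average at every age | proportional to the exposed | 0.920 | 1.00 |

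The last row shows that a ratio below five, or one that varies without relation to age, causes no bias. Within each age band the RR is 1, so adjustment for age at entry removes this part.

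**Set against the effect sought.** A true RR of 0.75 multiplied by 1.16 appears as 0.87. With the power formula above, p0 = 0.003349/0.87 = 0.003849, and power falls from 92% to Φ(−0.43), about 33%. Multiplied by 0.90, a true 0.75 appears as 0.68, which exaggerates the effect.

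**Would the 10% rule catch it?** Moving from 0.917 to 1.00 is a change of 9.0% of the crude value or 8.3% of the adjusted one, below the threshold on either base. Moving from 0.902 to 1.00 is 10.8% or 9.8%, so the result depends on the base. Moving from 1.16 to 1.00 is 13.8% or 16.0% and would be caught, provided that age is offered to the rule.

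**The case against.** The strongest reply is that the Protocol is silent rather than wrong. It excludes neither conditioning on the sets nor an age term, and relying on matching is compatible with an analysis that uses the matched sets. Such detail commonly sits in a statistical analysis plan, which is not at hand. It is therefore right that nobody should infer that the model expressly ignores matched sets. What remains is that the Protocol makes a positive statement about how age and sex are handled, and that statement is insufficient for the model it names. A later plan that followed the two sections literally would inherit the gap.

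Second, the bullet on age and sex stands within the list of covariates to be explored, and the sensitivity analysis covers all potential confounders. A reader might infer that the plan has no means of detecting or correcting the problem. The text does not support that; it is unclear whether age and sex are offered to the stepwise rule. Even if they are, a bias below 10% can pass, and age at entry does not correct for unequal follow-up.

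Third, neither match completeness nor follow-up by group is given, so every scenario above is an illustration. This stands in full.

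**Conclusion.** The point holds as a badly fixed rule. Matching at entry is presented as sufficient, the named model does not make it so, and the Protocol ensures neither condition under which it would be.

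The size rests on assumed values. With an 8% rise in PD rate per year of age and a true RR of 1, the apparent RR is 0.92 for 5 versus 7 years of follow-up, and 1.16 or 0.90 for the two ratio patterns. Neither the sign nor the size in this study can be known from the Protocol.

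Three stronger readings are not supported. One is that the primary result will be biased, or biased in a given direction: confounding is possible, not shown. Another is that any unequal matching ratio causes bias: the ratio must be related to age or sex. The third is that age is the strongest PD risk factor: the Protocol says only that it is a known one.

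**What to change.** In Statistical Analysis, state that follow-up will be split by current age in narrow bands, and that current age and sex will be fixed terms in every Poisson model, outside the stepwise rule. The alternative is to condition on the matched set and add current age. In Exposures, Outcomes and Covariates, replace the sentence that leaves age and sex to matching with one that names both the matching and these model terms. Calendar year, already a listed covariate, can be made a fixed term too, but this point does not depend on it.

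The cost is some person-time splitting and a change of wording, with no new data. The loss of precision is negligible. With full 1:5 matching and no effect, 144 + 5×144 = 864 events would be expected. That figure does not apply if matching is incomplete: under the assumptions above, 5/5/4/3 gives 144 + 144×3.411/0.920, about 680, and 3/4/5/5 gives 144 + 144×4.386/0.920, about 830. Either is ample for a few age terms and one for sex.
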